### Side-effect measurement

The most widely used measurement of VR related side-effect was the Simulator Sickness Questionnaire (SSQ), developed by Kennedy et al. [50]. The SSQ consists of 16 items with answers ranging from 0 to 3 based on the severity of the participant's symptoms. The SSQ includes three subscales: nausea, oculomotor and disorientation. The overall score serves as an indicator of total severity of the simulator sickness, with a higher the SSQ score indicating more severe simulator sickness [39]. The Chinese version of SSQ showed acceptable structure validity and reliability [51].

### Data collection procedure

The Consolidated Standards of Reporting Trials flowchart is presented in Fig. 4. The research nurse who is responsible for participant recruitment and random group assignment will carry out baseline evaluations. Each participant will be required to complete the Chinese versions of the IBQ, HADS, BIPQ, EORTC-QLQ C30 and the socio-demographic questionnaires at colorectal oncology ward. Data collection will be carried out through electronic questionnaires distributed to discharged participants by a research nurse who will remain blinded to the group allocation of the participants. Immediately following the program's final session, another research nurse will conduct semi-structured interviews with the participants in VR-CBT group. If the research nurse fails to reach some participants, their main caregivers will be contacted and remind the participants to complete the follow-up.

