### Sample size and recruitment

The primary outcome of the sick role adaptation in this study was used to calculate the effect size. Given the little published data on the effectiveness of VR-assisted CBT on the sick role adaptation among cancer patients, the sample size was calculated using PASS 15.0 based on a prior study in which a CBT intervention was delivered to elderly inpatients and yielded a s statistically significant improvement in the sick role adaptation. The mean score of the sick role dimension of the intervention group was (4.8 ± 1.2) and (6.6 ± 1.5) of the control groups. A sample size of 23 participants per group, assuming a more moderate effect size of 0.5, is predicted to provide the study with 95% power at a 1% level of significance to detect an effect size of at least 0.5 for the study's primary outcome of the sick role adaptation following the intervention. There will be a need for a total of 60 participants, with 30 in each arm, assuming a 20% attrition rate.

Eligible participants will be recruited through poster advertisements in wards and referrals from physicians. Then they will be approached by a research nurse who will distribute information sheets detailing the VR-CBT app and relevant consent forms. Prior to randomization, baseline data will be collected after receiving written consent. Data for follow-up will be collected at 1, 2 and 3-month after the completion of the 7-week sessions to examine the sustainability of the effects. The recruitment of participants will be completed by December 2023. Once recruited, patients will be randomly assigned to the VR-CBT group or AC group.

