### Randomization and blinding

Participants will be assigned to the VR-CBT group or AC group using a stratified randomization, with an allocation ratio of 1:1, to ensure the equal distribution in colon cancer and rectum cancer patients throughout the recruitment period. A random sequence of grouping identifiers will be produced in advance using computer-generated random numbers by a researcher who does not participate in the trial and determine the eligibility of the subjects. According to the enrollment order and the associated group identifier in the previously created random sequence list, the group allocation for each participant will be distributed consecutively. Because of the nature of psychological interventions adopted in the study, it is difficult to conceal participants and the researchers who administer the intervention, researchers who will assess the outcomes will be blinded solely and not be notified of the group status of the participants.

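### Recruitment, baseline evaluation and group assignment are given to the same research nurse, so concealment of the next allocation is not protected as written

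*Protocol article*

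**What the plan says.** Three sections of the protocol article bear on this point.

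- **Randomization and blinding.** Allocation is made "using a stratified randomization, with an allocation ratio of 1:1, to ensure the equal distribution in colon cancer and rectum cancer patients". The sequence is computer-generated in advance "by a researcher who does not participate in the trial and determine the eligibility of the subjects", which I read as someone who neither takes part in the trial nor judges eligibility. It is then applied to one patient after another: "According to the enrollment order and the associated group identifier in the previously created random sequence list". Only those who assess outcomes are to be blinded.
- **Sample size and recruitment.** A research nurse approaches eligible patients and hands out the information sheets and consent forms. On timing: "Prior to randomization, baseline data will be collected after receiving written consent".
- **Data collection procedure.** "The research nurse who is responsible for participant recruitment and random group assignment will carry out baseline evaluations". Follow-up questionnaires are distributed "by a research nurse who will remain blinded to the group allocation of the participants".

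**The concern.** Generating a sequence and concealing it are separate safeguards. An independent generator ensures that the sequence is random. It does not stop the person who enrols patients from knowing which group comes next. Protection against that depends on who holds the sequence and when each code is released.

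Here the stated division of roles puts recruitment and assignment in the same hands. If the recruiter knows or can find out the next code, the decision whether to approach a particular patient, or when to complete that patient's enrolment, can depend on it. No ill intent is needed: a nurse who thinks a motivated patient would do well with the app may simply prefer to enrol that patient at a particular moment. The groups would then differ systematically from the start.

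The stakes are higher than usual because the trial has few other defences. The Limitations section accepts that participants cannot be blinded. The primary outcome, sick role adaptation on the Illness Behavior Questionnaire, and the secondary outcomes are questionnaires that participants complete. A blinded nurse who distributes questionnaires gives no protection against groups that were unlike at entry.

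**Working it through.** No figure stated in the plan decides this point, so the check is to set the passages side by side and follow one patient through the process.

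1. **The sequence exists before the patient does.** Under Randomization and blinding, the list is produced in advance and followed in enrolment order. The next allocation is thus fixed before the next patient is approached.
2. **A research nurse approaches the patient and handles consent.** This stands under Sample size and recruitment. Data collection procedure confirms that recruitment is a research nurse's responsibility.
3. **The recruiting nurse carries out the baseline evaluation.** Data collection procedure says so.
4. **The same nurse is responsible for the random assignment.** The same sentence says so.
5. **Search for a barrier between steps 1 and 4.** Randomization and blinding makes the generator independent but does not say who holds the list afterwards. No section says how or when a code reaches the nurse. The rule that baseline precedes randomization sets the order of events for each patient. It does not hide a code that was fixed at step 1.
6. **Search for text showing that the nurse sees the codes.** There is none. Being responsible for assignment is compatible with asking someone else for each code.

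Steps 1 to 4 are stated. Steps 5 and 6 together mean that concealment may or may not exist in practice, but the roles as written do not secure it.

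**Could the analysis repair it?** Data analysis lists sex, age, monthly income per capita, family history of cancer, stage of cancer and time as covariates in the generalized estimating equations model. These are recorded characteristics. Steering would plausibly act on things that are not recorded, such as willingness to engage or the nurse's impression of how a patient is coping. Adjustment for the listed covariates does not remove that, and baseline homogeneity tests cannot show its absence.

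**Scale.** Planned size is 60 patients, 30 per arm, with 23 per arm as the calculated number before attrition. One patient is 1/30 = 3.3% of a randomized arm, or 1/23 = 4.3% of an arm of 23. These fractions show how few enrolments need be affected to matter. They are not an estimate of bias. An estimate would need the number of enrolments affected and how far those patients differ from the rest, and the document gives neither.

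**The case against.** The strongest defence is that the sequence comes from a researcher outside the trial, that nothing says the nurse can read it, and that envelopes, list custody and code release are details a journal article commonly leaves to the full protocol. That defence stands against any claim that allocation is unconcealed. It does not dispose of the point, because the criticism rests on something the article states: recruitment and assignment belong to the same nurse. If the full protocol separates them, the sentence in the article is wrong and should be corrected. If it does not, the arrangement should change.

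Three stronger readings are tempting, and the document does not support them.

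- **That randomization is simple, from a single list, and balance by site is not delivered.** A reader might infer this from the singular word for the list and from consecutive allocation. The same section states stratified 1:1 randomization "to ensure the equal distribution in colon cancer and rectum cancer patients throughout the recruitment period". Any stratified scheme allocates consecutively within its strata, so the two statements are compatible. Probabilities of colon or rectum imbalance calculated on the single-list reading would rest on an assumed site split and an assumed absence of restriction, and none would apply if stratification is carried out as stated. I therefore give none.
- **That the follow-up nurse may be the assigning nurse.** A nurse who assigns groups cannot remain blinded, so the text already implies a different person. Saying so outright would be a clarification of wording only.
- **That baseline measures are open to influence.** The plan places baseline before randomization, and participants complete the questionnaires themselves. This route is weak; the main exposure is selection of who is enrolled and when.

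**Conclusion.** The point holds in a limited form. As written, the nurse who recruits and does baseline evaluations also assigns groups from a sequence fixed in advance, and only the generation of that sequence is independent. Concealment of the next allocation from the recruiter is therefore not protected. This exposes the primary comparison to selection bias in an open-label, single-centre trial of 60 patients with self-reported outcomes.

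The conclusion rests on the stated roles, and on the assumption that the unshown full protocol does not assign them differently. It does not rest on any claim that the nurse has seen codes, and it implies nothing about whether the stratification works. The size of the bias is unknown; what can be said is that it could not be reliably removed afterwards. The change is worth making because it is cheap and removes the exposure at its source.

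**What to change.** Amend Data collection procedure so that the nurse who recruits and takes baseline measures does not assign groups. Amend Randomization and blinding to say that the independent researcher who generates the sequence also holds it, and releases one code at a time only after that patient's consent and completed baseline have been logged. The code should be drawn from the colon or rectum list according to tumour site, so that the stated stratification is visibly applied. A clause saying that the follow-up nurse is a different person from whoever learns the allocation could be added at the same time.

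The cost is a few sentences and one message per enrolment, 60 at the planned size. The small downside is that a researcher described as not participating in the trial takes on a continuing code-release task, so that description needs a matching exception. If enrolment has already begun, the procedure actually used should be documented, including who held the sequence and when codes were released.

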**Fig. 4 Fig4:**
[figure not shown]
The Consolidated Standards of Reporting Trials flowchart

All data will be stored on a secure and password-protected database, which will be accessible to the principal researchers involved in the study for the purpose of analysis and reporting. Review of data collected by other researchers is not permitted. Original documentation and signed informed consent forms will be kept in lockable file cabinets.

### Data analysis

Data will be analyzed using IBM SPSS 26.0 (IBM Corp.). Demographic data will be described and presented with appropriate statistics, including frequency distributions, means with standard deviations, medians with interquartile ranges. In the case of skewed variables, appropriate transformations will be applied prior to their inclusion in the inferential analysis. The outcome analysis will adhere to the intention-to-treat principle. The homogeneity of baseline characteristics between the two groups will be assessed using appropriate statistical tests including independent *t*- test, chi- squared test or Fisher's exact test. The study will apply the generalized estimating equations model adjusting for specific covariates (sex, age, monthly income per capita, family history of cancer, stage of cancer, and time), to compare the changes in each outcome variables between the two groups across different time points. Multiple imputation will be adopted to handle missing data. All statistical tests employed in this study will be two-tailed, with a significance level set at 0.05.

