**Methods:**

This is an assessor-blinded, randomized controlled trail that adheres to the SPIRIT 2013 Statement guidelines. A total of 60 working-age CRC patients will be recruited from the colorectal wards of a cancer center and randomly assigned to the VR-CBT group or attention control (AC) group. The VR-CBT group will receive a 7-sessions VR-CBT targeted to sick role adaptation, while the AC group will receive weekly attention at the same time the VR-CBT group receives the intervention. The sick role adaptation, anxiety and depression, illness perceptions, and quality of life will be measured at baseline, 1, 2 and 3-month after completion of the intervention. Side-effects related to VR in the VR-CBT group will be measured at the end of each session. The participants will receive invitations to participate in semi-structured interviews to explore their experiences with the intervention.

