### Other measurements

The socio-demographic and clinical characteristics of the participants will be collected, such as sex, age, educational level, marital status, household income per month, tumor location, stage and treatment modality.

Furthermore, semi-structured interviews will be employed to explore and gain insights into participants’ experiences and perceptions of the VR program until data saturation. The post-intervention interviews will be carried out following the completion of the final scheduled session and audio recorded after obtaining informed consent from the participants. Open-ended, probing questions will be used to guide the interview (Table 2). Content analysis approach will be applied to analyze the qualitative data.

**Table 2 Tab2:** Topic guide for post-intervention interview

1. When do you usually use the app? Why? 2. How do you feel about VR program? 3. What impressed you most in the VR program? 4. How the VR program help you adapt to the sick role and cope with CRC? 5. Have you experience any discomfort or difficulties during the usage of the VR program? Please tell me details. 6. What are your thoughts on the homework? 7. What advice would you give us on the VR program? 8. If there is a chance, would you recommend the VR program to other patients? Why?	

In addition, login counts and time, length of usage, time spent of each session, quiz results and results of human–computer interaction will be collected via backend monitoring data to evaluate the completion of the intervention. On the other hand, the privacy issues will also be seriously taken into account. First, the app will not collect the personal information that may recognize the patient identity such as name, age, residence and diagnosis. Second, the user data will be stored in password-controlled, restricted-access servers in the university to protect user information from loss, misuse, unauthorized access or disclosure, alteration, or destruction. Third, the user behavior data will only be used for statistical analysis and supervised by the Institutional Review Board of School of Nursing, Sun Yat-sen University.

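### The fixed GEE covariate list leaves out the stratification factor (colon or rectum) and does not condition on baseline scores: valid, but less precise than the collected data allow

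*Protocol article*

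**What the plan says.** - **Design.** Under Randomization and blinding, patients are allocated "using a stratified randomization, with an allocation ratio of 1:1, to ensure the equal distribution in colon cancer and rectum cancer patients". Tumour site is therefore a design factor.
- **Data available.** Other measurements lists "tumor location, stage and treatment modality" among the characteristics recorded. According to the abstract, the outcomes "will be measured at baseline, 1, 2 and 3-month after completion of the intervention". The Data collection procedure section has the baseline questionnaires completed on the ward.
- **Model.** Under Data analysis, the GEE is fitted "adjusting for specific covariates (sex, age, monthly income per capita, family history of cancer, stage of cancer, and time", in order "to compare the changes in each outcome variables between the two groups across different time points". The list is closed: no wording marks it as a set of examples.
- **Size and error rate.** Sample size and recruitment states "There will be a need for a total of 60 participants, with 30 in each arm". Data analysis sets two-sided tests at 0.05, intention-to-treat and multiple imputation.
- **Not stated.** The text does not say whether baseline is a response or a covariate, which variance estimator is used, or which reference distribution.

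**The concern.** The list adjusts for five patient characteristics on which randomisation was not stratified, and leaves out the one on which it was. It also leaves out what is usually the strongest predictor of a follow-up score, the same score at baseline. With 60 patients, precision is scarce. At the standardised difference of 0.5 that the plan names as its target, a simple two-group comparison has about 48% power with 30 per arm, or 40% with 24 per arm. Any precision that can be recovered from data already collected therefore matters.

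**Working it through.** **Inputs.** From the protocol: 30 per arm, difference d = 0.5 SD, two-sided alpha 0.05, one baseline and three follow-up measurements. Assumed, because the protocol gives no figure: r = 0.3, 0.5 or 0.7, and equal variance at each visit.

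**The plan's own figure.** The protocol gives no figure for the precision of its model. Its 95% power with 23 per group at 1% significance does not follow from d = 0.5, where power is 17 to 19% at the 1% level. The 23 does follow from the prior-study means: d = 1.8/√((1.2² + 1.5²)/2) = 1.8/1.358 = 1.325. That is a separate matter. Here d = 0.5 is used only because the plan names it as the effect to detect.

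**Step 1, baseline.** For a single visit, in units of the outcome variance:

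- change from baseline: 2(1 − r)
- conditioning on baseline: 1 − r²
- ratio: (1 − r²)/(2(1 − r)) = (1 + r)/2

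Power comes from the noncentral t with 58 df, the effect being 0.5 divided by the square root of the variance factor.

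| r | change factor | baseline-adjusted factor | ratio | power, change | power, adjusted |
|---|---|---|---|---|---|
| 0.3 | 1.40 | 0.91 | 0.65 | 36% | 51% |
| 0.5 | 1.00 | 0.75 | 0.75 | 48% | 59% |
| 0.7 | 0.60 | 0.51 | 0.85 | 69% | 76% |

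The normal approximation gives 37 to 53%, 49 to 61% and 71 to 77%. With 24 per arm the t-based figures are 30 to 43%, 40 to 50% and 59 to 66%.

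If the GEE instead used only the follow-up scores, with no baseline, the variance factor would be 1 and power 48% at any r. The adjusted column is unchanged, so the gain would be about 3, 12 or 28 points.

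**Step 2, tumour site.** A constant site effect cancels from a within-patient change, so adding site to a change model cannot help much. Simulation (3,000 to 4,000 trials per setting, r = 0.5, exchangeable working correlation, the listed covariates, assumed site effect 0.5 SD) gives these average single-visit standard errors:

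| Model | N | site omitted | site included |
|---|---|---|---|
| change (group-by-time) | 48 | 0.281 | 0.281 |
| change (group-by-time) | 60 | 0.253 | 0.253 |
| follow-up only | 48 | 0.289 | 0.278 |
| follow-up only | 60 | 0.260 | 0.250 |

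The cost is nil in the change model and about 4% in the follow-up-only model (0.289/0.278 = 0.260/0.250 = 1.04).

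The null rejection rate of the uncorrected single-visit test at N = 48 is 6.2% without site and 6.4% with it in the change model. In the follow-up-only model it is 6.2% without and 8.4% with. Omitting site therefore does not inflate the error; where it has an effect, it lowers it.

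**Step 3, small-sample behaviour, if the robust variance were left uncorrected.** Null rejection at nominal 5%, N = 60, no site effect:

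| Model | single visit | 3-df joint test |
|---|---|---|
| change | 5.6% | 6.5% |
| follow-up only | 6.6% | 8.2% |
| follow-up with baseline covariate | 6.4% | 8.1% |

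With the Mancl-DeRouen variance and a t or F reference, the same settings give 3.5 to 4.6%. Monte Carlo error is about 0.3 to 0.4 points.

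**The case against.** Three objections carry weight.

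- **Baseline is probably not ignored.** A reader might infer from the list that the plan has no baseline control. The text does not support that: the model is said to compare changes across time points and baseline is one of the measurement times, so it most naturally enters as a repeated response. A comparison of changes is unbiased in a randomised trial. What stands is a loss of efficiency, plus an ambiguity about how baseline enters. The size of the loss depends on an unknown r and falls to about 7 points of power at r = 0.7.
- **The stratum matters little numerically.** A reader might infer that omitting it costs power and distorts the standard errors. Step 2 shows no cost in a change model, a small cost otherwise, and an error in the conservative direction. What stands is the principle that the analysis should reflect the randomisation.
- **The test is not shown to be liberal.** A reader might infer that a GEE in 60 patients gives wrong error bars. The article names no variance estimator or reference distribution, and such details may properly sit in an analysis plan that is not shown. Multiple imputation under intention-to-treat also keeps the analysed number near 60 rather than 48, where the excess is modest. Step 3 therefore supports a precaution, not a fault in the plan.

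In addition, if the true effect were as large as in the prior study (d = 1.325), power with 30 per arm would exceed 99% at a variance factor of 1. The gain would then show only in narrower intervals.

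**Conclusion.** The point holds as one of efficiency and of consistency with the design. The closed covariate list omits the stratification factor and does not condition on the baseline outcome, although both are collected. The material part is baseline: conditioning would cut single-visit variance by 35, 25 or 15% for r = 0.3, 0.5 or 0.7 against a change analysis, worth about 15, 12 or 7 points of power at d = 0.5 and 30 per arm. These figures rest on the assumed r, equal variances and a single visit, and they ignore any precision gained from the other covariates. The omission of tumour site is a departure from the design with little numerical consequence. Neither omission makes the planned analysis invalid, and an inflated type I error is not established by the text.

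**What to change.** Before any comparison by group, amend the Data analysis text as follows:

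1. Take the 1, 2 and 3-month scores as the responses. Include group, visit, group-by-visit, the baseline value of the same outcome and tumour site (colon or rectum), plus the covariates already listed.
2. Include tumour site and the baseline scores in the imputation model, so that it matches the analysis model.
3. As a secondary precaution, state a small-sample correction: for example the Mancl-DeRouen variance with a t or F reference, or a REML repeated-measures model with Satterthwaite or Kenward-Roger degrees of freedom.

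No new data, patients or procedures are needed. The cost is two more model terms and, with the correction, slightly larger p-values.
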